#### Overall project evaluation

A mixed methods approach with survey feedback and qualitative interview will be conducted to understand primary care satisfaction with the software including usability, feasibility, and implementation.

### Data collection and management

Three years of historical primary practice data will be collected (historical control) and compared with three years of active intervention. Primary practice data will be extracted from the primary care electronic medical record and FHT database in a non-re-identifiable format using software Grhanite™ [14]. Grhanite™ software enables data linkage without needing re-identification of patient data [14]. FHT usage will be extracted from the FHT monitoring system. Hospital utilisation, including admission and outpatient attendance to relevant specialties will be extracted from the hospital electronic record system. Hospital data will be converted to a non-re-identifiable format using Grhanite™ prior to being provided to the research team and then subsequently linked to the primary care data. All data will be housed on a secure server. Survey data will be collected using REDCap electronic survey and data capture tools hosted by Western Health [15, 16]. REDCap is a secure web-based software platform designed to support data capture for research studies [15, 16]. Practice interviews will be recorded and transcribed using a voice-to-text function, and then manually checked for accuracy.

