**Methods:**

This pre-post implementation trial using an interrupted time series design will evaluate the clinical and service outcomes of Future Health Today, using a mixed methods study in twenty general practices with an estimated population size of 150,000. Deidentified patient data will be extracted from participating practices to examine the primary aims of the study. Surveys and semi-structured interviews with general practice will inform secondary hypotheses. Data linkage between primary care and tertiary care data will examine the broader health service impacts.

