## Methods

### Study design

This will be a pragmatic implementation trial using an interruptive time series design comparing outcomes in the three years prior to trial commencement with three years of active trial. Primary care data will be linked with tertiary care administrative data to enable analysis of broader health service impact. The overall program evaluation will use a mixed methods approach using the clinical performance feedback intervention theory framework [12].

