### Outcomes

Primary outcome: change in the number of patients who are meeting quality of care indicators in three domains:

Screening: an appropriately timed kidney health check in patients at risk of kidney disease.Diagnosis: total number of patients with coded diagnosis of CKD.Management: patients with CKD on a renin angiotensin system inhibitors with at least 12 months follow up following a CKD diagnosis.

Secondary outcomes: these are divided into patient centric, health centric and overall evaluation.

Patient centric secondary outcomes:

1.1 Change in number of patients achieving the kidney cycle of care. This involves monitoring of renal function, albuminuria, diabetes (if diabetic), fasting lipids and blood pressure measurement.1.2 Change in proportion of patients on any antiproteinuric medication including angiotensin converting enzyme inhibitor (ACE inhibitor) or angiotensin receptor blocker (ARB), sodium glucose co-transporter 2 inhibitor (SGLT2 inhibitor) and mineralocorticoid antagonists (MRA). With sub analysis of each medication class.1.3 Change in proportion of patients with type two diabetes and CKD prescribed an SGLT2 inhibitor.1.4 Change in urinary albumin to creatinine ratio (uACR) in patients with CKD diagnosis and at least 12 months follow up.1.5 Change in slope of estimated glomerular filtration rate (eGFR) in patients with a coded diagnosis of CKD compared 2 years prior and 2 years post and adjusted for baseline function. The index date will be CKD diagnosis coded or if CKD already diagnosed at entry into study.1.6 Subgroup analysis: Subgroup analysis will be undertaken comparing those with a coded diagnosis of CKD, to those with measured CKD (all patients meeting CKD diagnostic criteria) and possible CKD (patients who have one eGFR or uACR in diagnostic criteria). This will be conducted as CKD is well known to be under coded in the medical health record. CKD will be defined according to the Kidney Disease Improving Global Outcomes criteria [13].1.7 Potential further subgroup analysis will be conducted with frequent, moderate, and minimal users of FHT (if a difference is found between practices).

Health centric secondary outcomes:

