### Data analysis

Descriptive statistics will be used to describe the baseline characteristics in the historical control and active group. Primary end points will be calculated, and a chi square test will be used to assess if the difference between pre and post-test is significant for the primary outcomes (nominal data), with *p* < 0.05 considered significant.

Univariate analysis will be undertaken for each of the outcomes to compare differences in the characteristics of the historical control versus the three year active intervention. For continuous variables, the data will be tested for normality using Shapiro Wilk test and equality of variances using Levene’s test. If these assumptions hold true, parametric tests like the t-test or ANOVA will be used. If these assumptions do not hold then nonparametric alternatives will be considered. For categorical variables a Chi Squared test will be used. When comparing multiple groups, post hoc investigations may be included with Bonferroni corrections. Regression models will be used to control for co-variates.

The analysis will be undertaken 3 years prior to study commencement (historical control) and then interim analysis yearly until trial conclusion.

Survey responses will be analysed to understand the usability of FHT software and if practice staff felt the software aided their management of CKD. Semi structured interviews of practice champions and additional primary care physicians will be conducted via zoom or phone, according to interviewees preference. Interview transcripts will be coded by at least two researchers. The clinical performance feedback intervention theory framework will be used for the overall implementation evaluation combining survey and interview data [12].

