Earlier detection and management of CKD requires time for improvements to be realised, hence a three-year trial duration was chosen. One limitation of a pre-post implementation trial with a historical control is the inability to assess direct causation. This approach was chosen given the practical challenges of a randomised trial in primary care over three years in addition to the ethical challenges of preventing practices from undertaking quality improvement and CKD educational activities over this extended duration. To help address this limitation an interrupted time series design has been chosen with a 3-year retrospective control compared to the 3-year prospective intervention used to assess the rate of change in parameters over time. This will assist in determining if improvements are due to a natural increase in screening, diagnosis, and management over the course of time, or associated with the intervention.

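### Data collection and the pre-period cover the same three years, so a rolling screening status would have no look-back at its start and could show a false pre-FHT rise

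*Protocol article*

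**What the plan says.** Under Data collection and management, the protocol article sets the data window: "Three years of historical primary practice data will be collected (historical control) and compared with three years of active intervention". Study design uses the same span as the comparison period, "comparing outcomes in the three years prior to trial commencement with three years of active trial". The Discussion uses it again as a "3-year retrospective control compared to the 3-year prospective intervention used to assess the rate of change in parameters over time", and relies on that comparison to separate a natural increase in screening, diagnosis and management from an association with the intervention. Records from before those three years are not mentioned anywhere.

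The Screening domain of the primary outcome is "an appropriately timed kidney health check in patients at risk of kidney disease". The article does not give the check interval.

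Under Data analysis, "a chi square test will be used to assess if the difference between pre and post-test is significant for the primary outcomes". On timing, the same section says: "The analysis will be undertaken 3 years prior to study commencement (historical control) and then interim analysis yearly until trial conclusion". The spacing of the time-series points and the rule for dating a patient's screening status are not stated.

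**The concern.** Whether a check is in date on a given day depends on tests before that day. If nothing before the first pre-period day is held, a patient tested shortly before it counts as unscreened. The observed proportion then starts near zero and rises until the data cover one full check interval. On the first day of the FHT period three years of records already lie behind, so ascertainment there is complete. One of the three primary domains could therefore be measured differently in the two periods.

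The artefact falls on the pre-period trend. The Discussion concedes that a historical control cannot show direct causation and offers the rate of change before FHT as the safeguard. An artificial early rise would damage that safeguard, and it would push the two kinds of analysis in opposite directions:

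- a comparison of averaged levels would show a gain that did not occur;
- a segmented regression would project too steep a pre-trend and could hide a real gain or suggest harm.

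The measured-CKD subgroup (Outcomes, item 1.6) has the same exposure. It separates patients who meet the diagnostic criteria from those with only one qualifying result, so earlier results decide the class.

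**Working it through.** The article gives no screening rate, interval or power figure, so there is nothing of its own to reproduce. What follows is an illustration with no FHT effect.

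**From the article.** Historical data: 36 months. Pre-period: the same 36 months. FHT period: 36 months.

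**Assumed (not in the article).** True in-date coverage c is constant at 30–50%; the testing rate is constant; the check interval L is 12 or 24 months; data begin at month 0 of the pre-period.

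**Formulas.** Rate λ = −ln(1 − c)/L per month. Observed coverage at month m = 1 − exp(−λ·min(m, L)). Once m reaches L this equals c.

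**Monthly points, c = 50%, L = 12.** λ = 0.6931/12 = 0.0578. Observed coverage is 5.6% at month 1, 29.3% at month 6 and 50% from month 12. The first 12 months average 29.9%, so the pre-period mean is (12 × 29.9 + 24 × 50)/36 = 43.3%, which is 6.7 points low.

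**Monthly points, c = 50%, L = 24.** λ = 0.6931/24 = 0.0289. Observed coverage is 2.8% at month 1, 29.3% at month 12 and 50% from month 24. The first 24 months average 28.9%, so the mean is (24 × 28.9 + 12 × 50)/36 = 35.9%, which is 14.1 points low.

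The segmented columns below come from a least-squares fit to months 1–72 with a break after month 36. The true values are all zero.

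| L (months) | c | Pre mean | Shortfall (points) | False pre-slope (points/yr) | False step (points) | False slope change (points/yr) |
|---|---|---|---|---|---|---|
| 12 | 30% | 25.7% | 4.3 | +6.8 | −5.6 | −6.8 |
| 12 | 50% | 43.3% | 6.7 | +10.7 | −8.9 | −10.7 |
| 24 | 30% | 21.0% | 9.0 | +10.4 | −6.2 | −10.4 |
| 24 | 50% | 35.9% | 14.1 | +16.6 | −10.2 | −16.6 |

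The FHT-period mean equals c in every row, so the shortfall is also the false pre/post gain.

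**Yearly points (months 12, 24, 36).**

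- L = 12: all three points equal c, so the shortfall is 0.
- L = 24, c = 30%: 16.3%, 30%, 30%; mean 25.4%, shortfall 4.6 points.
- L = 24, c = 50%: 29.3%, 50%, 50%; mean 43.1%, shortfall 6.9 points.

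**One status at the end of each period (months 36 and 72).** For any L up to 36 months both equal c, so the shortfall is 0.

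**With the remedy.** If records for a further L months before the pre-period are available, min(m + L, L) = L at every point. Observed coverage is then c throughout, and the shortfall, slope, step and slope change are all 0.

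**The case against.** The strongest reply is that the article does not establish the conditions the artefact needs. The three-year statement may simply name the comparison period; nothing says that earlier test dates are excluded when status is set. The check interval, the extraction date range and the dating rule are details that an article can leave to the full protocol or analysis plan. No section specifies monthly points, and the only cadence given is baseline and then yearly. The chi-square test for nominal data also fits one status per patient per period at least as well as an average over many points. Under that reading both periods are 36 months long and are treated alike.

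Most of this stands. A reader might infer that pre-FHT screening is bound to look low and rising, and that the Screening outcome is distorted whichever analysis is used. The article does not support that: with yearly points and a 12-month interval, with end-of-period status, or with earlier test dates in the extract, the effect is zero.

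The reply does not remove the point. The window is something the article states, three times and consistently, and a later analysis plan cannot use records that were never extracted. The layouts free of the artefact also sit uneasily with the Discussion: one status per period gives no pre-trend, and three yearly points give a thin one. Yearly points with a 24-month interval still leave the first year low.

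**Conclusion.** The point holds conditionally. As written, collection and pre-period share one three-year window, so the start of the screening series has no look-back while the FHT period has it in full. This matters if three things are true together: status is rolling, the points are closer together than the check interval, and no earlier test dates are held.

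In that case averaged levels are biased toward FHT and a segmented fit is biased against it. The size runs from 0 to 14.1 points on the pre-period mean, according to the interval (12 or 24 months) and the spacing (monthly, yearly or end of period). With monthly points the false pre-slope is about +7 to +17 points per year. All of this rests on the assumed 30–50% coverage, a constant testing rate and no FHT effect. No size was derived for the measured-CKD subgroup.

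**What to change.** State the check interval. Extract test and diagnosis records for one full interval (the longest one used) before the three-year pre-period, and use them only to set status at each point, not as extra pre-period outcome data. Apply the same look-back to the measured-CKD subgroup.

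If earlier records cannot be obtained, start the screening series one interval after data begin. The price is a shorter pre-series: 36 − 12 = 24 months with a 12-month interval, or 36 − 24 = 12 months with a 24-month one.

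The preferred change needs a longer date range in the extraction and no extra patients or visits. The article does not say which dates the ethics approval and consent waiver cover, so this should be checked before the range is extended. If the full protocol already provides for earlier test dates, one sentence saying so settles the matter.

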#### Exclusion criteria

Sites without the technical infrastructure to support the Future Health Today platform (the platform works with commonly used practice software Best Practice and Medical Director). Patients identified as having a renal transplant or dialysis will be excluded from the primary analysis.

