#### Recruitment

 Recruitment will take place at the practice level and will focus on practices who have been identified to serve a patient population with a significant burden of chronic disease with complex care needs. These practices have been identified through a hospital program to support patients with high risk of hospital re-admission in the context of chronic disease. Recruitment will then be expanded to the broader tertiary centre catchment area as required.

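### The only test named for the primary outcomes is a pre/post chi-square with no practice or time term, so it would mistake a change in practice mix for an effect if practices contribute unequally to the two periods

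*Protocol article*

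**What the plan says.** All references are to the protocol article.

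- **Periods.** Study design describes "comparing outcomes in the three years prior to trial commencement with three years of active trial". Data collection and management repeats this: "Three years of historical primary practice data will be collected (historical control) and compared with three years of active intervention". Neither sentence says how records from different practices are combined.
- **Primary test.** Data analysis states that "a chi square test will be used to assess if the difference between pre and post-test is significant for the primary outcomes", with p < "0.05 considered significant". It mentions no practice stratum, pairing or time term.
- **Other analysis text.** The next paragraph of Data analysis, on univariate comparisons, ends by promising regression to adjust for covariates. It names no covariates and does not tie the regression to the primary outcomes. Study design and the Discussion call the design an interrupted time series, and the Discussion relies on it to separate the intervention from natural improvement. Data analysis contains no time series model.
- **Outcome scale.** Outcomes defines the primary outcome as "change in the number of patients who are meeting quality of care indicators in three domains", which is a count.
- **Practices.** The abstract gives "twenty general practices with an estimated population size of 150,000". The only site exclusion is "Sites without the technical infrastructure to support the Future Health Today platform". Recruitment starts with practices identified through a hospital program, and "Recruitment will then be expanded to the broader tertiary centre catchment area as required".

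**The concern.** A chi-square on a pre/post two-by-two table compares one pooled proportion with another. It does not set each practice against its own history. The pooled difference equals the within-practice change only if the mix of practices is the same in both periods, or if practices do not differ in level.

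The article leaves room for the mix to change. Eligibility does not require three usable historical years. Recruitment may be widened later, and the periods are tied to trial commencement without saying whether that date is common or set per practice. Practices from the two recruitment sources may also differ in baseline level.

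If the mix did change, the primary result would partly describe which practices supplied data. This affects the point estimate, so a standard error corrected for clustering would not remove it. The test also has no time term, so it counts any background improvement as effect, which is the risk the Discussion says the time series is there to address.

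**Working it through.** **Inputs from the article.** 20 practices; 150,000 patients, so 150,000 / 20 = 7,500 per practice on average; three years on each side; chi-square at 0.05. The article gives no indicator rate, practice drop-out or between-practice variation, so there is no figure of its own to reproduce.

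**Assumed inputs.** Practices of equal size, no effect of the software, and each practice's rate the same before and after. Of the 20 practices, k lie g points below the rest (rate r) and supply only a share w of the active period.

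**Formula.**
- Pre = r − g·k/20
- Post = r − g·kw/(20 − k + kw)
- False change D = g·[k/20 − kw/(20 − k + kw)]

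With w = 1, D = 0: equal contribution gives no mix bias.

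**Practices stopping at month 12** (w = 12/36; r = 45%; g = 20; 3,000 at-risk patients each, so 60,000 pre records):
- k = 1: pre (19×45 + 25)/20 = 44.0%; post (855 + 8.33)/19.33 = 44.7%; D = +0.7 points, p = 0.02.
- k = 2: pre (18×45 + 2×25)/20 = 43.0%; post (810 + 16.67)/18.67 = 44.3%; D = +1.3 points. With 56,000 post records, z is about 4.4 and p about 0.00001.
- k = 4: pre (16×45 + 4×25)/20 = 41.0%; post (720 + 33.33)/17.33 = 43.5%; D = +2.5 points.

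**Range.**
- Smallest case (k = 1, g = 10, exit at month 24): 10×[0.05 − 0.667/19.667] = 0.2 points.
- Largest case (k = 4, g = 20, no active data): 20×4/20 = 4.0 points.

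**Direction.** If the leavers lie above the rest, g is negative and D changes sign. Two leavers at 65% give pre (810 + 130)/20 = 47.0%, post (810 + 43.33)/18.67 = 45.7%, D = −1.3 points. Two practices with no history, 20 points above or below the rest, shift the result by 20×2/20 = 2.0 points in that direction.

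**Count scale.** In the k = 2 case the number meeting the indicator falls from 0.43×60,000 = 25,800 to 18×1,350 + 2×750/3 = 24,800, while the proportion rises by 1.3 points.

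**Second set of assumptions.** Practice rates are evenly spread over 45–55%, 40–60% or 30–70%, with 750 or 7,500 eligible patients per practice.
- The two lowest-rate practices lose all active data: D = 0.53, 1.05 and 2.11 points. Pooled p = 0.37, 0.076 and 0.0004 at 750 per practice, and 0.005, 2e-8 and 3e-29 at 7,500.
- Two practices lost at random (2,000 simulated trials per scenario): the pooled chi-square rejects in 6%, 12% and 29% of trials at 750, and in 23%, 48% and 72% at 7,500. A Mantel-Haenszel test stratified by practice rejects in about 4–5%.

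All p-values and rejection rates here treat pre and post records as independent. The false change D does not depend on that.

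**Why stratifying is not enough.** Assume a background rise of 1 point a year. The midpoints of two adjoining three-year periods are 3 years apart, so a stratified pre/post contrast shows about 1×3 = 3 points with no effect. Time terms are needed as well.

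**The case against.** The strongest reply is that the trigger is hypothetical. The article plans three years on each side, and under that plan the mix bias is exactly zero. History is taken retrospectively from the practice record, so late recruitment does not by itself remove it. A practice that stops using the software need not stop supplying data. Two recruitment sources with different baseline levels do no harm if every practice is in both periods. All of this stands.

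A reader might go further and infer that the article commits to pooling practices with unequal data, or that its silence on practice withdrawal is an error. The text supports neither. The sentence in Data collection and management only sets the periods, and rules for practice withdrawal may sit in a fuller protocol or analysis plan. An all-positive range would also mislead, because it assumes that only low performers leave.

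It can also be said that the regression sentence and the interrupted time series mean the chi-square is not the whole analysis. That is fair, but neither removes the problem. The regression is not linked to the primary outcomes and names no practice term. The time series has no model in Data analysis, and one fitted to pooled totals would have the same weakness.

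**Conclusion.** The point holds in conditional form. The article names one test for the primary outcomes, and that test ignores both practice and time. It is therefore exposed to practice mix and does not match the interrupted time series on which the Discussion relies.

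Mix bias arises only if practices contribute unequally to the two periods and differ in baseline level. Under the assumptions shown, losing 1 to 4 of 20 practices moves the pooled proportion by roughly 0.2 to 4 points in either direction. With tens of thousands of records, shifts near 1 point can reach significance. On the count scale any lost practice lowers the active-period number, so the count and the proportion can move in opposite directions.

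The actual size cannot be derived from the article, and nothing in it shows that such bias will occur. The change is still worth making, because the weakness lies in a stated method and costs little to remove.

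**What to change.** In Data analysis, replace the chi-square as the primary test with a within-practice interrupted time series regression. Model the proportion of eligible patients meeting each indicator. Enter practice as a fixed effect or stratum, with terms for pre-existing trend, level change and slope change, so that each practice's active period is set against its own history. State the denominator for each domain, since the diagnosis domain is now a total number. Keep the chi-square as descriptive only.

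Add a sensitivity analysis limited to practices with complete data in both periods. It also helps if practices differ in trend, because shared slope terms could then still respond to mix.

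The cost is mainly analysis wording and the denominator definitions; the planned extraction already covers both periods. The small downside is that practices with only one period add little or nothing to the primary contrast.
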